### Randomisation

Randomisation will be performed by institution at the FACT team level. Through this cluster-randomisation, contamination between the experimental and control groups can be avoided [35]. Before participants are included, the participating FACT teams will be randomly assigned to either the smoking cessation intervention (intervention group) or usual care (control group). The randomisation will be performed by an independent statistician, who is not involved in the execution of the study, using a computer-generated list of random numbers. Due to the nature of the intervention and the study design, the blinding of patients and FACT team members will not possible.

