**PATIENT REPORTS**				
Symptoms of depression and anxiety (HADS)	x		x	x
Positive and negative symptoms (PANSS-6)	x	x	x	x
Substance Use (WHO-ASSIST)	x		x	x
Cannabis Questionnaire	x		x	x
Health-related self-efficacy (PAM-13)	x		x	x
Quality of life (SF-12)	x		x	x
Self-report physical activity (PA)	x		x	x
**DEMORGAPHICS**^a^				
Age, gender	x			
Education level	x			x
Marital status	x			x
Employment status	x			x
Diagnosis of SMI	x			x
Number of years receiving mental care	x			x
Medication use	x			x

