### Statistical analysis

The characteristics of people with SMI in the intervention and control groups will first be presented at baseline and using descriptive statistics (mean [standard deviation], median [range], or frequencies [percentage]). All analyses will be conducted on an intention-to-treat basis, including all randomised patients in the groups to which they were allocated where data are available.

To compare the effects of the intervention with those of usual care on CO-verified smoking cessation (primary outcome) between baseline and 3, 6, and 12 months, a mixed model with a three-level structure (observations clustered within patients, patients clustered within FACT teams, and FACT teams clustered within institutions) will be used, including a random intercept the patient, FACT team, and institution levels [52]. The necessity of random slopes will be assessed using the likelihood ratio test, which will compare the model with random intercepts with a model with random intercepts and random slopes.

The first model will be an ‘overall’ model, with only the treatment variable included. This will provide information about the treatment effect of the primary outcome (odds ratio, 95% confidence interval, and *p*-value), which can be interpreted as the average overall treatment effect over time. Subsequent analyses will include a categorical variable for time (as a dummy variable) as well as an interaction between treatment and time to enable an in-depth investigation of the intervention’s effects at different time points [52].

For binary secondary outcome variables, a similar analysis strategy to the one above will be used. For continuous variables, we will run the first model as mentioned as well as use a longitudinal analysis of covariance to appropriately adjust for the baseline value of the outcome variable [53].

All of the aforementioned models will be additionally adjusted for prognostic variables to increase the precision of the crude treatment effects [54]. These prognostic variables will be identified through a literature study and directed acyclic graphs (DAGs) [55].

Finally, a descriptive analysis will be performed to compare the number of cigarettes smoked per day over time between the two groups as well as attendance at group sessions within the intervention group.

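### Binary secondary outcomes inherit a model with no baseline value, built for an outcome that is constant at entry; for any outcome that varies at baseline this costs power and lets arm differences carry through

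*Protocol article*

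**What the plan says.** All of this is in the Protocol article, mainly under Statistical analysis.

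- The smoking-cessation strategy starts from a treatment-only model: "The first model will be an ‘overall’ model, with only the treatment variable included". Its estimate is to be read as the average treatment effect over time. Then: "Subsequent analyses will include a categorical variable for time (as a dummy variable) as well as an interaction between treatment and time". No baseline covariate is named in either step.
- Binary secondary outcomes are sent to the same place: "For binary secondary outcome variables, a similar analysis strategy to the one above will be used".
- Continuous outcomes get the treatment-only model too, but the analysts will also "use a longitudinal analysis of covariance to appropriately adjust for the baseline value of the outcome variable". The article does not say which of the two estimates is the reported effect.
- A general clause follows: "All of the aforementioned models will be additionally adjusted for prognostic variables to increase the precision of the crude treatment effects". The variables are to come from literature and directed acyclic graphs; none is named.
- Under Participants, being a current smoker is an entry criterion. Cannabis and other substance use are not fixed by eligibility, and a primary diagnosis of cannabis use disorder is explicitly allowed.
- Table 1 schedules the WHO-ASSIST and the cannabis questionnaire at baseline, 6 and 12 months.
- Under Randomisation: "Before participants are included, the participating FACT teams will be randomly assigned". Patients and team members are not blinded, and under Recruitment the treating professionals then select and approach patients.

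**The concern.** A model without a baseline term suits smoking cessation because baseline status is the same for everyone, so there is nothing to adjust for. The reason disappears once the model is lent to an outcome on which patients already differ before treatment. For such an outcome the baseline value is usually the strongest single predictor of the follow-up value. Omitting it leaves avoidable variance in the estimate, and any difference between the arms at entry passes into the treatment effect in proportion to how strongly the outcome tracks over time.

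The authors accept this argument for continuous outcomes in the very next sentence. Nothing in the article explains why a binary outcome should be treated differently. At stake is the reading of secondary results such as substance use, in a trial with about 13 teams per arm and recruitment after allocation. The primary outcome is not affected.

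**Working it through.** **The plan's own figures.** The article gives no number for binary secondary outcomes. Its primary-outcome figure reproduces if two-sided 5% and 80% power are assumed (neither is stated): n = [1.96·√(2 × 0.225 × 0.775) + 0.842·√(0.30 × 0.70 + 0.15 × 0.85)]² / 0.15² = 120.5, so 121 per group. Also 127/0.8 = 158.75, so 159 per arm and 318 in total. These fix the scale of the trial for the check below.

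**Inputs from Sample size.** 12.7 teams per arm, taken as 13; 10 patients per team; ICC 0.05, used as the team-level share of latent variance.

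**Assumed inputs.** Baseline prevalence 40%; latent correlation between baseline and follow-up of 0.5, 0.7 or 0.9; one follow-up.

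**Model.** Each patient has latent value = team effect + patient effect + visit error, with total variance 1, and is a user if it exceeds 0.253 (giving 40%). A treatment effect of −0.45 on the latent scale moves follow-up prevalence from 40% to 1 − Φ(0.703) = 24%, about −16 points. A persistent pre-existing shift of +0.26 moves one arm from 40% to 1 − Φ(−0.007) = 50%, about +10 points at both visits.

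**Analysis.** 1,500 simulated trials per scenario. Linear-probability fits with cluster-robust standard errors compare follow-up on treatment with follow-up on treatment plus baseline value. Monte Carlo error is about √(0.05 × 0.95/1500) = 0.6 points near 5% and √(0.65 × 0.35/1500) = 1.2 points near 65%.

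Each cell shows without → with the baseline value.

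| Correlation | SD of estimate, no effect | Rejection, no effect, no imbalance | Power, −16 points | Spurious effect, persistent imbalance | Rejection, persistent imbalance |
|---|---|---|---|---|---|
| 0.5 | 0.069 → 0.062 | 4.9% → 5.4% | 65.1% → 75.7% | 10.4 → 7.1 points | 28.9% → 18.3% |
| 0.7 | 0.068 → 0.055 | 5.7% → 5.1% | 65.4% → 81.7% | 10.5 → 5.3 points | 30.9% → 14.9% |
| 0.9 | 0.070 → 0.045 | 5.3% → 5.6% | 68.1% → 94.3% | 10.3 → 3.1 points | 29.8% → 10.1% |

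**Carry-over of chance imbalance.** With no effect and no systematic imbalance, each 1-point baseline difference moved the unadjusted estimate by 0.48, 0.60 and 0.76 points. The baseline difference itself had an SD of about 7 points, so a one-SD chance gap shifts the estimate by 0.48 × 7 = 3.4 to 0.76 × 7 = 5.3 points.

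**Why adjustment is only partial under persistent imbalance.** At correlation 0.5 it removes 10.4 − 7.1 = 3.3 points. A single yes/no baseline reading measures the underlying tendency imprecisely, so the rest stays in the treatment coefficient.

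**The other reading of the model.** The article compares arms from baseline to the follow-ups, so baseline might be kept as an outcome row. With baseline, 6 and 12 months and a constant effect d at both follow-ups, the treatment-only coefficient on a linear scale averages (0 + d + d)/3 = 0.67d. The effect is diluted by a third, and any baseline gap is averaged in as well.

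**The case against.** The strongest reply has four parts.

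1. **No binary secondary outcome is declared.** Most are scales or continuous measures, and the WHO-ASSIST and cannabis questionnaire may be analysed as scores, in which case the existing analysis of covariance covers them. This stands and limits the scope. A reader might infer that cannabis, other substance and e-cigarette use are all planned binary secondary outcomes. The article does not say so, and Table 1 lists e-cigarette use under smoking.

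2. **The plan leaves room.** The strategy is only *similar*, and the prognostic adjustment could include the baseline value. It could, but the article does not say so. The clause adds models on top of the crude ones, so the crude estimates remain as they are. The same clause applies to continuous outcomes, where the authors still thought it necessary to name baseline separately.

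3. **Baseline as an outcome row.** The treatment-by-time model could then separate the baseline difference from the change. That is correct for the interaction model. It does not rescue the treatment-only overall model.

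4. **Randomisation already protects the comparison.** A reader might infer that the unadjusted analysis is biased, or that false rejection is generally inflated. Without systematic imbalance it is neither: the simulation gives no bias and about 5% rejection. The 29–31% depends on a 10-point difference set by hand. With an SD of about 7 points, a gap of 10 or more in either direction arises by chance in only about 15% of trials (z = 10/7 = 1.43). A reader might equally infer that baseline adjustment restores the 5% level. It does not when the pre-existing difference is persistent.

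**Conclusion.** The point holds in limited form. For any secondary outcome that is analysed as binary and varies at entry, the stated strategy is weaker than the one the same paragraph gives continuous outcomes, and the baseline data are already scheduled.

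The main cost is power: about 65–68% against 76–94% for an effect of about −16 points. The range reflects the assumed correlation, and the effect size, 40% prevalence and use of the smoking ICC are likewise assumptions. The simulation also simplifies the planned repeated-measures logistic model to one follow-up on the risk-difference scale, so its figures show direction and rough size only.

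False attribution is a secondary risk. A persistent difference is plausible because unblinded teams recruit after allocation, but nothing in the article shows that one will occur. If it does, adjustment helps (about 29–31% down to 10–18% rejection) without curing it.

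The primary outcome, the sample size and the main conclusion are untouched. For continuous outcomes the planned longitudinal analysis of covariance already captures most of the gain; what remains is to say that its estimate is the reported one.

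**What to change.** In Statistical analysis, replace the sentence on binary secondary outcomes with wording such as:

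> For each binary secondary outcome, the mixed logistic model will be fitted to the follow-up measurements and will include the outcome's baseline value as a covariate, in the overall model as well as in the model with time and treatment by time. For binary and continuous secondary outcomes, the baseline-adjusted estimate is the reported effect.

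Any treatment-only estimate for these outcomes should be dropped or labelled descriptive. It would also help to state which secondary outcomes, if any, will be analysed as binary.

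The cost is a sentence or two and no new data. There are two small downsides: the odds ratio becomes conditional on baseline status, and patients with a missing baseline value need a stated method. The smoking-cessation model needs no change on this account.

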### Handling of missing data

A study demonstrated that mixed models are suitable in situations of longitudinal data with some missing data, in principle averting the need for imputation methods [52]. However, a sensitivity analysis will be run for patients who were allocated to the intervention arm but did not receive any treatment. This sensitivity analysis will include a selective multiple imputation mixed model as described and advised by Twisk et al. [56].

All analyses will be conducted using StataCorp SE version 16.

## Discussion

Smoking among people with SMI is highly prevalent and strongly associated with poor health. Given the high morbidity and mortality rates in individuals with SMI due to diseases directly linked to smoking, an urgent need exists for innovative evidence-based smoking cessation interventions that can be incorporated into mainstream mental health care delivery. This is even more crucial as intervention programmes targeted at the general population do not connect with the needs of people with SMI. This urgent need has been advocated by both researchers and policy makers [57–60] and supported by recommendations from national [61] and international guidelines [62–64]. Moreover, mental health institutions have a great need for effective innovative intervention programmes, including recommendations for successful implementation strategies. Therefore, this study aims to evaluate the implementation and effectiveness of a smoking cessation intervention, compared with usual care, in people with SMI treated by FACT teams in the Netherlands (KISMET).

A strength of this study is the application of a qualitative method (i.e., a Delphi study) to design the intervention before the start of the clinical trial. We established the intervention protocol based on recent scientific findings regarding helpful therapeutic elements for smoking cessation for people with SMI, combined with expert opinions on the contents, structure, and considerations for implementation [36]. Another strength is that a pragmatic study design has been employed, which means that the implementation and evaluation occur in a real-life setting. The outcomes of this study will offer direct insights into the feasibility, acceptability, and effectiveness within current clinical practice, in which we aim to offer the treatment after its effectiveness has been established through this trial. Therefore, the results of this trial will form reliable grounds for formulating clinical implications and recommendations for smoking cessation support in Dutch ambulatory mental health care. An adaptation of this intervention in other countries would possibly require a few adjustments with the consideration of local guidelines for tobacco addiction treatment in the mental health care sector as well as health insurance policies regarding reimbursement for such a treatment. Moreover, the content of the group sessions should be culturally adapted by, for instance, adjusting for distinct attitudes towards smoking.

The recruitment during this trial might pose a challenge. First, recruiting mental health institutions and affiliated FACT teams is difficult, especially in light of the ongoing burden imposed by COVID-19 on the mental health sector and the nationwide introduction of a new funding system. Second, participating FACT teams might encounter difficulties with the inclusion of patients. Recruitment in mental health trials is a common challenge [65]. Therefore, a clear recruitment strategy is essential for including an adequate number of participants. Based on the outcomes of the SCIMITAR trial in similar settings [66], the most critical aspects for successful recruitment are the motivation of MHCPs to support patients in their efforts to quit smoking and their relationship with their patients [67]. A strong therapeutic alliance can positively affect quitting and maintaining abstinence, which is potentially explained by more mutual trust, closer collaboration, and the exchange of positive emotions. These characteristics of a strong therapeutic relationship can facilitate open communication about challenges and difficulties.

Alongside the RCT, we will also conduct a process evaluation at the patient and mental health care professional levels through in-depth interviews. The overall aim is to examine barriers, facilitators, experiences, and perspectives regarding implementation. This approach will combine both quantitative RCT outcomes with qualitative process evaluation outcomes, thereby increasing the internal validity of this study. Thus, we will gain a comprehensive understanding of the working mechanisms of this intervention’s implementation. This will aid in establishing recommendations for further developing the intervention and strategies for (more) effective implementation. Another objective of the process evaluation is to identify relevant aspects for future research as well as how to more effectively promote innovation within the mental health care sector.

Offering a smoking cessation intervention to patients with SMI and training MHCPs to deliver it can empower both patients and professionals. Patients will have the opportunity to learn the required skills and supporting tools for dealing with their tobacco addiction as well as be able to gain more awareness of their own (unhealthy) behavioural patterns. This could increase their self-efficacy and -management of their own physical and mental health. The additional training that the MHCPs will receive could boost their confidence as care providers through increasing their ability to support patients with smoking cessation, thereby improving their somatic and mental health.

Moreover, the experience of successfully implementing a smoking cessation intervention and potentially obtaining positive treatment outcomes could reduce treatment pessimism regarding tobacco addiction. This could in turn alter attitudes based on the stigma that people with SMI are less capable of quitting or do not wish to quit smoking compared with people without SMI.

In light of recent developments, including more attention and efforts allocated to lifestyle promotion within mental health care, we believe that this intervention will contribute to the body of knowledge on ‘lifestyle psychiatry’ and provide insights into the impact of smoking on mental health. We have specifically included secondary outcomes on mental health (i.e., symptoms of anxiety and depression as well as psychotic symptoms) to understand the relationship between smoking, smoking cessation, and mental health and whether it is in line with current literature, which indicates an improvement of mental health after smoking cessation [12].

Overall, this study will provide relevant information on the barriers to and facilitators of the implementation and effectiveness of a smoking cessation programme for people with SMI treated in Dutch ambulatory psychiatric care. If the programme is proven to be feasible and effective, the results will offer a unique venture point for the implementation and its dissemination into ambulatory mental health care. In addition, practical implications will be provided for further policymaking regarding tobacco use as well as future research objectives. These objectives include improving the feasibility and integration of lifestyle-promoting programmes in mental health care. The first results of this trial are expected in 2024.

## Data Availability

Not applicable.

## Abbreviations

BMI: Body mass index
CBT: Cognitive behavioural therapy
CO: Carbon monoxide
FACT: Flexible Assertive Community Treatment
FTND: Fagerström Test for Nicotine Dependence
HADS: Hospital Anxiety and Depression Scale
MHCP: Mental health care professional
PA: Physical activity
PAM-13: Patient Activation Measure
PANSS-6: Positive and Negative Syndrome Scale
RCT: Randomised controlled trial
SF-12: Short-Form Health Survey
SMI: Severe mental illness
WHO-ASSIST: World Health Organization – Alcohol, Smoking and Substance Involvement Screening Test
